### Power calculation

Our pilot data using the Clinical Record Interactive Search (CRIS) database (the anonymised Case Register^26^ local to King’s College Hospital, London) revealed the following for 20 perinatal women on generic acute wards, 20 admitted to MBUs and 20 under CRTs: acute ward patients were most likely to be readmitted to these services with 95% being readmitted at some point during 12-month follow-up, compared with 35% of women who received MBU care; CRT readmission rates were similar to MBUs. Therefore, assuming similar readmission rates nationally for MBU patients (35%), we could detect a doubling of risk for generic acute ward patients with 90% power with 47 women in each group. We aim to recruit 100 women in each group; to allow for 20% attrition and exclusion of women for being beyond the ‘region of support’ (ie, whose characteristics make them unmatchable with women in another treatment arm—see Statistical methods section for further details).

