## Analysis

### Statistical methods

There is limited availability of specialist MBU beds and it is, therefore, likely that some women who would be offered an MBU bed at first presentation are admitted to an acute ward, while waiting for a bed. As some women may also receive care from more than one type of inpatient service (ie, MBU and acute ward) during their index admission, in our main analysis MBUs will be classified as the ‘highest level of care’ and we will run two sensitivity analyses—one based the majority of days spent within a specific inpatient service and the other based on first service accessed.

We shall use a propensity score approach to account for systematic differences between MBU and non-MBU participants. This approach allows the exact specification of the covariate adjustment to be determined blind to the outcome data, thereby reducing the risk of unintended bias. The Stata command p score will estimate the propensity score of the treatment (MBU or non-MBU) on specified covariates, selected using problem knowledge and exploratory comparison of cohorts, using a probit model and will stratify individuals in blocks according to the propensity score. The blocks are determined by a balancing algorithm and the balancing property within each block is tested, to ensure sufficient blocks are used to adequately balance the covariates. We will also remove women with characteristics that place them beyond the ‘region of support’ and thus for whom there are no ‘matches’, that is, women with propensity scores either so high or so low that there are insufficient similar women receiving either MBU or non-MBU treatment to make a comparison; we will report characteristics and outcomes for these women separately.

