Once the propensity scores have been formed, they will be included in the primary and secondary analyses through use of the inverse propensity score weights^27^ (ie, weighted regressions will be performed), which will also be combined with the inverse probability weights for drop-out, known as attrition weights, specific to each endpoint measure. The readmission rate will be modelled using logistic regression, with adjustment for baseline measures that are likely to increase power, that is, baseline measures of outcome and symptom severity. Point estimates, CI and significant tests based on the sandwich estimator of the parameter covariance matrix^28^ will be reported. Analysis on the primary outcome will include stratum specific treatment estimates. Trends in effect estimate over strata can be informative as to variability of effect, an advantage of using the stratification matching technique. The computation of average treatment effects will be restricted to the common region of support. Sensitivity analyses will also be performed.

We shall also examine geographical and temporal variation in MBU services as a source of instrumental variables to account for unmeasured selection effects.

Missing data will be accounted for on three levels: single imputation or prorating for sporadic missing item-level data that contribute to scores, multiple imputation for entirely missing scales or factors and listwise deletion for those with insufficient data to allow plausible imputation.

Sensitivity analyses will examine the impact of different treatment arm definitions, formed following an examination of the observed treatment pathway patterns.

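### Passing significance tests inside small propensity blocks does not show that the covariates are adequately balanced; judge the propensity model on the size of imbalance in the weighted sample

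*Protocol article*

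**What the plan says.** Under Statistical methods, a probit model "will estimate the propensity score of the treatment (MBU or non-MBU) on specified covariates". Women are then stratified by the score. "The blocks are determined by a balancing algorithm", and the stated purpose of the check that follows is to confirm balance: "the balancing property within each block is tested, to ensure sufficient blocks are used to adequately balance the covariates". The article states no other criterion for accepting the score, and gives no number of blocks and no significance level for these tests.

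The score is then used beyond the blocks: "Once the propensity scores have been formed, they will be included in the primary and secondary analyses through use of the inverse propensity score weights". The weights are combined with attrition weights. The logistic model for readmission also adjusts for baseline measures of outcome and symptom severity, average effects are restricted to the common region of support, stratum-specific estimates are reported, and instrumental variables are to be examined.

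On numbers, the Power calculation section says: "We aim to recruit 100 women in each group; to allow for 20% attrition and exclusion of women" outside the region of support.

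**The concern.** The study is not randomised, so control of measured confounding depends on how well the propensity model is specified. The article treats non-rejection within blocks as the assurance that the specification is good enough. A non-significant test in a small block is weak evidence of balance. The rule also has an awkward property: each further split of the blocks lowers the power of each test, so splitting can turn a fail into a pass without removing any imbalance.

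The tests also look in the wrong place for the main result. The primary estimate comes from the inverse-propensity-weighted sample, and a pass within blocks does not describe balance there. If a specification is accepted with material imbalance left in a prognostic covariate, the weights carry that imbalance into the primary and secondary estimates, and the stratum-specific estimates carry it too. The covariates most exposed are those outside the severity and baseline outcome measures already in the outcome model.

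**Working it through.** **The plan's own figure.** The article gives no figure for the balance tests. Its sample-size figure reproduces: 35% v 70%, 90% power and two-sided 5% (the level is assumed) give 40.7 per group, and 46.2 with continuity correction, which rounds up to the stated 47. It is not in dispute.

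**Inputs.**
- From Power calculation: 100 women in each of three groups. The score contrasts MBU with non-MBU, so the target is 100 v 200. Taking the 20% allowance as loss gives 80 v 160.
- Assumed: 5 equal blocks (range 3 to 10); two-sided test level 5% or 1%; a two-sample t-test on one continuous covariate; imbalances of 0.5 and 0.25 SD.

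**Formula.** For a block with n1 MBU and n2 non-MBU women and a true difference of d SD, the test statistic is noncentral t with n1 + n2 − 2 degrees of freedom and noncentrality d × √(n1·n2/(n1 + n2)). The miss rate is the probability that it falls between the two critical values.

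**Worked case, 16 v 32 (80 v 160 in 5 blocks), d = 0.5.** Noncentrality = 0.5 × √(512/48) = 1.63 on 46 df. Critical values are 2.01 (5%) and 2.69 (1%). Miss rates are 64% and 84%.

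**Miss rate for 0.5 SD in one block.**

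| Setting | Block | 5% level | 1% level |
|---|---|---|---|
| 100 v 200, 3 blocks | 33.3 v 66.7 | 35% | 60% |
| 100 v 200, 4 blocks | 25 v 50 | 48% | 72% |
| 100 v 200, 5 blocks | 20 v 40 | 57% | 79% |
| 80 v 160, 5 blocks | 16 v 32 | 64% | 84% |
| 80 v 160, 10 blocks | 8 v 16 | 80% | 93% |
| Uneven block | 5 v 43 | 82% | 94% |
| 80 v 160, no blocking | 80 v 160 | 5% | 15% |

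At the 10% level with 5 blocks of the full sample, the miss rate is 44%. The same imbalance is missed more often simply because the block is smaller.

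**Imbalance present in every block (80 v 160, 5 blocks).** The chance that all five tests pass is the single-block miss rate to the fifth power.
- d = 0.25: 0.874⁵ = 51% (5% level); 0.963⁵ = 83% (1% level).
- d = 0.5: 0.641⁵ = 11%; 0.842⁵ = 42%.

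**Possible size of the effect.** This is an illustration only. It assumes an odds ratio of 2 per SD for readmission, a covariate not in the outcome model, and an imbalance that carries over unchanged to the weighted sample. Starting from 35%:
- 0.5 SD in one of five equal blocks averages 0.5/5 = 0.10 SD overall. OR = 2^0.10 = 1.07, so 35% becomes 36.6%.
- 0.25 SD throughout: OR = 2^0.25 = 1.19, so 35% becomes 39.0%.

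**Where a size limit can be applied.** The standard error of a standardised difference is about √(1/20 + 1/40) = 0.27 in a 20 v 40 block, and √(1/100 + 1/200) = 0.12 in the whole unweighted sample. A 0.10 limit is unworkable block by block. It belongs on the whole weighted sample.

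**The case against.** The strongest reply is that the block tests carry less weight than this suggests. The primary estimate uses weights, adjustment for severity and baseline outcome measures, and restriction to common support, and instrumental variables are examined as well. This stands. A reader might infer that the whole causal comparison rests on the block tests, and the article does not support that.

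A reader might also infer that a 0.5-SD imbalance would usually pass and would then bias the result badly. That joins two different situations. In a single block it often passes, but averages only about 0.10 SD overall. In all five blocks it would pass everywhere only 11% of the time at the 5% level (42% at 1%). A shift from 35% to 43% (odds ratio 2^0.5 = 1.41) needs 0.5 SD across the sample in a covariate left unadjusted, so severity is a poor example. Nor does 'usually' hold with 3 or 4 full-size blocks at the 5% level.

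The tests can also be too strict. With 15 covariates in 5 blocks (assumed), perfect balance and independent tests at the 5% level, all 75 pass with probability 0.95^75, about 2%. This is a fair limit on the miss rates, which concern one covariate at a time. It does not defend the rule: the outcome still turns on block size and the number of tests.

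Finally, balance diagnostics are ordinary content for an analysis plan, and none is shown. The absence of standardised differences from a condensed article is therefore not the finding. The finding is the inference the article does state, that testing within blocks ensures adequate balance.

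**Conclusion.** The stated criterion is unsound: a pass within propensity blocks does not establish adequate balance. On the central assumptions (80 v 160, 5 equal blocks) a 0.5-SD imbalance in one block is missed about two times in three at the 5% level and five in six at the 1% level. A moderate 0.25-SD imbalance running through every block is more likely than not to pass the whole procedure, narrowly at the 5% level and clearly at 1%. These rates rest on an assumed number of blocks and test level, and they fall with fewer, larger blocks.

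The consequence is possible residual confounding in the weighted primary and secondary estimates and in the stratum-specific estimates, chiefly from prognostic covariates beyond those already adjusted for. The documents do not show that such imbalance will occur, and they do not support a claim of large bias. The point merits a change because a better criterion is available at almost no cost.

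**What to change.** In Statistical methods, replace the within-block test as the criterion for accepting the propensity model:

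- Judge the model, blind to outcome, on the absolute standardised mean difference of every covariate in the score, calculated in the inverse-propensity-weighted sample within the common region of support.
- Use one target, 0.10, for all covariates. It limits the imbalance observed in the analysed sample, and should not be applied within blocks.
- If the target is missed, respecify the score with interactions or non-linear terms.
- Enter any covariate still above 0.10 in the outcome model.
- Keep the within-block tests as description only.

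This fits the article's own aim of fixing the covariate adjustment without sight of outcomes. The Study status section has primary outcome collection running to spring 2019, so at the time of the article the change could still be made before outcomes were linked. It needs no new data: a change of wording and a few lines of code. The small downside is some respecification work and possibly a few extra covariates in the outcome model.

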**Methods and analysis:**

Quasi-experimental study of women accessing different types of acute psychiatric services in the first year after childbirth. Analysis of the primary outcome will be compared across the three service types, at 1-year postdischarge. Cost-effectiveness will be compared across the three service types, at 1-month and 1-year postdischarge; explored in terms of quality-adjusted life years. Secondary outcomes include unmet needs, service satisfaction, maternal adjustment, quality of mother–infant interaction. Outcomes will be analysed using propensity scoring to account for systematic differences between MBU and non-MBU participants. Analyses will take place separately within strata, defined by the propensity score, and estimates pooled to produce an average treatment effect with weights to account for cohort attrition.

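### The Abstract and the Methods describe different propensity-score estimators, and the only balance check stated fits the stratified one, not the weighted one

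*Protocol article*

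**What the plan says.** The Abstract (Methods and analysis) gives this route to the treatment effect: "Analyses will take place separately within strata, defined by the propensity score, and estimates pooled to produce an average treatment effect". The only weights named there are for attrition.

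Analysis, Statistical methods, gives another. A probit score for MBU versus non-MBU care is estimated and women are grouped into blocks, where "the balancing property within each block is tested, to ensure sufficient blocks are used to adequately balance the covariates". The scores are then used as follows: "they will be included in the primary and secondary analyses through use of the inverse propensity score weights", that is, in weighted regressions, "which will also be combined with the inverse probability weights for drop-out, known as attrition weights, specific to each endpoint measure". For the primary outcome, "The readmission rate will be modelled using logistic regression, with adjustment for baseline measures that are likely to increase power", with sandwich standard errors.

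The same paragraph returns to strata: "Analysis on the primary outcome will include stratum specific treatment estimates". It says that trends over strata can show variability of effect, "an advantage of using the stratification matching technique". It gives no rule for pooling the strata and does not label either approach as primary or sensitivity.

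**The concern.** Pooling within-stratum estimates and inverse-propensity weighting use the same score in different ways. Stratification treats women in a block as comparable and leaves some confounding inside each block. Weighting uses each woman's own score, so it removes that coarseness but is sensitive to extreme scores. Bias, variance and possibly the estimated quantity differ. On the odds-ratio scale, pooled stratum odds ratios and an odds ratio from a weighted logistic model need not target the same number.

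The balance check follows from this. Its stated purpose is to decide whether there are enough blocks, so it validates the stratified estimator. If the Methods govern, the diagnostic that the article fixes belongs to a different estimator from the one giving the main result, and a score model could pass it while the weighted sample is unbalanced. The study is not randomised, so the credibility of the primary comparison rests on this adjustment.

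**Working it through.** **1. The two estimators side by side.** Let T be MBU care, e the propensity score and r the probability of remaining in follow-up.

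- Abstract: effect = Σ (n_k/n) × Δ_k over strata k, with each Δ_k weighted by 1/r. The share n_k/n is my assumption, as no pooling rule is stated.
- Methods: logistic regression of readmission on T and baseline measures, with weight [T/e + (1 − T)/(1 − e)] × 1/r.

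The factor in e is absent from the first and central to the second.

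**2. Why a block test does not speak for the weighted sample.** A block test compares covariate means with every woman counted equally. The weighted analysis does not count them equally. As an example, in a block of scores from 0 to 0.2, an MBU woman with e = 0.20 has weight 1/0.20 = 5 and one with e = 0.02 has weight 1/0.02 = 50, ten times as much. The relevant measure is the weighted standardised difference, |weighted mean in MBU − weighted mean in non-MBU| / √[(s₁² + s₀²)/2].

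**3. Sensitivity of a block test.** The target is 3 × 100 = 300 women. Less 20% attrition this is 240. Five equal blocks (assumed) hold 48 each, and with one third MBU that is 16 against 32. For an imbalance of 0.5 SD tested at 5% (level assumed): SE = √(1/16 + 1/32) = 0.306; 0.5/0.306 = 1.633; power ≈ Φ(1.633 − 1.960) = 0.37. Real blocks would be set by the balancing algorithm and would not all have a 1:2 ratio.

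**4. Size of the gap; illustration with all inputs assumed.** The documents give no covariate distributions, selection strength or block structure.

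Set-up A: 300 women, about one third MBU, three covariates, probit score, min–max support, five equal-width blocks without further splitting, block tests at 1%, no covariates in the outcome comparison, 1,500 runs per row. Risk differences are in percentage points.

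| Selection | Mean absolute gap | 90th percentile | Mean pooled | Mean weighted | Passing all block tests but weighted difference > 0.1 | Effective MBU sample |
|---|---|---|---|---|---|---|
| Weak | 2.5 | 4.7 | −12.0 | −14.3 | 42% | 70 of 89 |
| Moderate | 4.0 | 7.3 | −12.5 | −15.7 | 87% | 49 of 93 |
| Strong | 6.7 | 13.0 | −13.0 | −17.4 | 100% | 35 of 91 |
| Moderate, score misspecified | 6.7 | 12.6 | −12.4 | −18.1 | 97% | 33 of 87 |

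Effective sample is (Σw)²/Σw². Part of the weighted imbalance, mainly under weak selection, comes from the assumed min–max support rule and not from weighting as such.

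Set-up B: 240 women, no true effect, one confounder (probit slope 0.6, outcome log odds ratio 0.9), five blocks. Without covariates in the outcome model the mean gap was 3.4 points (90th percentile 6.4). With the confounder also in both outcome models, closer to the plan, it was 2.1 points (90th percentile 4.4). Each estimator's own sampling SD was 7 to 8 points. Against a midpoint of 7.5, the gaps are 3.4/7.5 = 0.45 and 2.1/7.5 = 0.28 of an SD.

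**5. The plan's own figure.** The sample size of 47 per group (35% versus 70%, 90% power) reproduces with a two-sided 5% test and continuity correction; the 5% level is assumed. It is 41 without the correction. It does not depend on the estimator, so no stated number changes.

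**The case against.** The Methods can be read as coherent on their own: weighted regression is the one method attached to the primary and secondary analyses, and stratum estimates are added to display variation in effect. On that reading the conflict is between a condensed abstract sentence and the detailed text, plus a loose phrase about stratification matching. This largely stands. It is why the point is not that two primary estimators have been fixed. It does not remove the mismatch, because the Abstract makes the pooled strata the source of the average treatment effect, and condensing a method should not replace it with another.

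A reader might also infer that the analysts could choose between the estimators after seeing both results. The article does not show that. It says the covariate adjustment can be specified blind to outcome, it names the weighted regression, and an unseen analysis plan may settle the choice.

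Weighted balance tables, effective sample size and weight distributions are routine content for such a plan, so their absence alone would be no finding. That stands too. The balance point survives only because the article does fix a diagnostic, and the one it fixes does not match the weighted estimator. It is the only check stated, which is not proof that no other is planned.

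The simulations are also not the plan. Block rule, support rule, selection strength and test levels are assumed, and most runs omit the planned baseline adjustment, which lowered the gap from 3.4 to 2.1 points in set-up B.

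**Conclusion.** The concern holds in a limited form. The Abstract and the Statistical methods section describe different estimators of the treatment effect and must be reconciled. The stated block test supports the stratified estimator and does not establish balance in the sample weighted as the Methods require.

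The likely size is moderate. Under assumed inputs the estimators differ by about 2 to 7 percentage points on average: about 2 with covariate adjustment in the one-confounder scenario, and nearly 7 with strong selection or a misspecified score and no adjustment. In the one-confounder scenario the gap is under half of one sampling SD. The direction of the conclusion on balance does not depend on the exact inputs; the percentages do.

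This is a change that should be made, at the lower end of that grade. It is not evidence that the primary result would be selected after the fact.

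**What to change.** - Before outcome data are examined, name one estimator as primary. The weighted logistic regression is the natural choice, since the Methods already specify its weights, model and standard errors. Make the pooled stratified estimate a sensitivity analysis, and state its pooling weights and effect scale.
- Align the Abstract with that choice, and describe the stratum-specific estimates as a display of variation in effect.
- Accept the score model on covariate balance under the weights that produce the estimate, including the attrition weights, and do not rely on within-block tests alone. Weighted standardised differences would serve; 0.1 is a conventional limit and not an essential one. Report effective sample size and extreme weights beside them.

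Either estimator would be acceptable as primary if it is named and its own balance is checked. The cost is a few sentences and one diagnostic table. The downside is that the score model may need another round of specification before outcomes are opened. No stated number changes.

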### Economic evaluation

We will evaluate whether MBU services are cost-effective in the short term (from index admission to 1-month postdischarge) and the longer term (from discharge from the index admission to 1-year postdischarge) in the treatment of women with severe mental illness following birth, compared with generic acute wards and CRTs. Analysis from admission to 12 months was not considered appropriate because lengths of index admission may vary greatly, which would heavily influence the total cost and thus the results of the cost-effectiveness analysis.

The economic evaluation at 1-month postdischarge will take the NHS and personal social services perspective preferred by NICE,^29^ with data collected in face-to-face interviews with participants using the Adult Service Use Schedule (AD-SUS) (see table 1 for full details of the AD-SUS measure). Since the index admission/acute care is the intervention, and since the development work indicated that this can be difficult for women to recall, data on this will be taken from clinical notes. The AD-SUS, therefore, focuses primarily on hospital and community-based contacts postdischarge from the index admission.

The economic evaluation at 1-year postdischarge will take a narrower mental health perspective, with mental health service use data collected from clinical records and the EuroQol five-dimension scale (EQ-5D-5L) collected via brief telephone interviews, given no face-to-face interviews with participants will take place at this time point. Resource use data for the period from the date of discharge from the index admission to the 1-year postdischarge follow-up will be collated using a proforma created by the research team and collected from secondary mental health records. The proforma was piloted and edited as needed to ease data completion. This proforma will include all contacts with secondary mental health services including further periods in MBU, generic acute ward or CRT care plus any outpatient or community mental health contacts. A briefer version of the proforma will be used to collect data on the use of key acute services (MBUs, generic acute wards or CRTs) in the 2-year period prior to the index admission.

Resource use data will be combined with unit costs from national published sources to calculate the total cost of participants admitted to the MBU, CRT and generic acute wards for the two different time periods (from index admission to 1-month postdischarge and from discharge from the index admission to 1-year postdischarge).

Costs and outcomes will be compared and presented in terms of mean differences and 95% CIs obtained by non-parametric bootstrap regressions (10 000 replications) to account for the non-normal distribution commonly found in economic data. Cost-effectiveness will be assessed through the calculation of incremental cost-effectiveness ratios^30^ and will be explored in terms of quality-adjusted life years (QALYs) calculated from the EQ-5D-5L^31^ and using the area under the curve approach.^32^ Utility data are not being collected at baseline as women are not being interviewed until after discharge from the index admission. We will, therefore, use published utility values for a similar population (women in crisis (eg, Howard *et al*
33)) as a substitute for utility at baseline. To provide more relevant treatment-effect estimates,^34^ all cost-effectiveness analyses will include prespecified covariates, in line with the main clinical analysis, plus the baseline variable of interest, where available. Uncertainty around the cost and effectiveness estimates will be represented by cost-effectiveness acceptability curves.^35^ The Short-Form Six-Dimension will be available at 1-month postdischarge and will be used to calculate QALYs to explore cost-effectiveness in the short term in a sensitivity analysis.^36^ Sensitivity analyses will also explore the impact of missing data.

